### Recruitment and Randomization

A continuous recruitment will occur through referrals from crisis teams of the entire county of Hordaland in Norway. Health care units of the general hospitals in Hordaland, as for instance emergency and intensive care units, will also recruit for this study to secure the inclusion of those who lose a family member to acute disease.

Bereaved partners will be informed about the study the first time they are in contact with the health care personnel immediately after the death, and potential participants will be given a study information brochure. They will then receive a phone call to schedule an appointment for a first meeting at their homes (or at our center if they prefer so). At the end of this first meeting, the families will receive a sealed opaque envelope containing information regarding their random group allocation. Randomization will be previously performed by an external and independent research assistant who will use blocks of 6 families (3 allocated to each arm of the trial) [34]. For each block of 6, containing 3 intervention condition cards and 3 control condition cards, the researcher will randomly draw a card assigning it to one family according to its order of entrance in the study. This will help to randomly vary the order of interventions within each block. Due to the nature of the intervention, it will not be possible to blind participants to group assignment. However, the researchers who visit and phone the families have no previous knowledge concerning allocation until the end of the first meeting. In addition, they will not be involved in the intervention phase.

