### Outcome Measures

SEIB consists of a complex intervention [45], designed to tailor both individual and family needs, that is expected to entail several interacting components and outcomes. Considering the relevance of SEIB’s intervention components in the almost immediate aftermath of a potential traumatic loss, we anticipate the primary outcome of SEIB refers to traumatic stress symptoms of both parents/children. The secondary outcomes of SEIB may refer to the individual level of complicated grief, psychological wellbeing, daily functioning, and social support in parents and children, while tertiary outcomes possibly refer to the parenting/family level and include parental capacity, parenting practices, and family functioning.

Given SEIB's initial focus on the potential misconceptions/maladaptive appraisals that usually follow a sudden death, and the early provision of trauma-reducing self-help methods, it is foreseen that SEIB may reduce traumatic stress symptoms of both parents/children. The reduction of this symptomatology may favor psychological wellbeing and optimize daily functioning, which in turn may strengthen the individual sense of self-efficacy and the ability to use the support from others within the social network, minimizing the chances for complicated grief. For the surviving parent, these conditions may set the stage for a more resourceful, stable, and organized parent more considerate of the child’s needs. Enhanced emotional availability in parents, combined with SEIB’s family perspective, may ultimately improve family functioning. Textboxes 2 and Textboxes 3outline the parent and child self-report measures that will be used.

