: The child self-report measuresChildren’s Impact of Event Scale (CRIES-8) [54] – assesses the subjective distress following a traumatic event. It is composed of 8 items rated on a 4-point scale ranging from ‘not at all’ (0) to ‘often’ (5).Inventory of Prolonged Grief for Adolescents (IPG-A) [55] – assesses symptoms of prolonged grief disorder. It is composed of 30 items rated on a 3-point scale ranging from ‘almost never’ (1) to ‘always’ (3).Strengths and Difficulties Questionnaire (SDQ) [56] – assesses psychological adjustment in children and adolescents. It is composed of 25 items rated in a 3-point scale ranging from ‘not true’ (0) to ‘certainly true’ (2), and an impact supplement focusing on functional impairment.Alabama Parenting Questionnaire (APQ) [52] – encloses a parent and child version. The equivalent items of the parent version will be used in the child version.Family Assessment Device (FAD) [53] – can be filled in from 12 -years -old onward. The same items will be used for both parent and child.

Measures were selected based on relevance, satisfying psychometric properties, brevity, and availability in the Norwegian language.

To assess both children’s and parents’ perspectives on the help and support they received following the death, we developed a self -report measure to relate their perception of SEIB and/or care as usual throughout their participation (Help Questionnaire).

As shown in Textbox 4, the families will be assessed at 4 time-points: baseline (T1), and after 3- (T2), 6- (T3), and 9-months (T4) follow-up. T1 will just comprise the use of two questionnaires: GHQ-12/SDQ and IES-R/CRIES-8. Given the closeness in time of T1 to the death, we expect the families to be acutely distressed at this time. Apart from T1, all the above-mentioned parent and child questionnaires will be included at the other time-points for assessment. These questionnaires will provide useful information on future power calculations and possible SEIB outcomes.

Assessment time-points and measures for all participants.T1: BaselineSociodemographicsParent: IES-R; GHQ-12Child: CRIES-8; SDQT2: 3 monthsHelp QuestionnaireParent: IES-R; ICG-19; GHQ-12; WSAS; CSS; PCS; APQ; FADChild: CRIES-8; IPG-A; SDQ; APQ; FADT3: 6 monthsSame as T2T4: 9 monthsSame as T2

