### Sample Size and Statistical Analyzes

In light of the small state of knowledge about early intervention in the aftermath of a potential traumatic death of a partner/parent, this study is not aimed to test SEIB effectiveness. Power analysis is not used to determine the final sample size, because it is not recommended for pilot studies that do not rely on inferential statistical tests [57]. Following a general rule of thumb that suggests the inclusion of 30 participants or more to determine a parameter (eg, mean/standard deviation) of an outcome variable [58], we will recruit a total of 60 families (30 families in each group). Rather than focusing on hypothesis testing, this pilot study builds on the practical limitations of recruitment and topics of incertitude, such as the need to gather initial estimations for sample size calculation [57,59,60].

Statistical analyzes will be computed using IBM SPSS Statistics and multiple imputation methods will be used to impute values of missing data [61]. Descriptive data will be computed to characterize the sample. On the basis that pilot study analyzes should be mostly descriptive and should provide confidence interval estimation [60,62], descriptive statistics (including mean, percent, standard deviation, and range), and confidence intervals will be used to describe all outcome variables at T1, T2, T3, and T4 providing important information regarding recruitment and randomization procedures, data collection forms, retention rates, future power calculations, and SEIB most appropriate outcomes.

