Given the acknowledged low power of pilot studies [57], an emphasis will be placed on evaluating indices of clinical significance. Independent of the normal distribution and sample size, the effect size estimation has been considered a strong predictor of clinically meaningful change in studies with small sample sizes [63]. Accordingly, Cohen’s *d* effect size of the differences in outcomes between groups and Cohen’s *d* effect size of change from baseline to follow-up will be performed and judged as follows: small (*d* ≥ 0.2), moderate (*d* ≥ 0.5), large (*d* ≥ 0.8), or very large (*d* ≥ 1.3) [64]. The preliminary early effects of SEIB will be addressed by comparing descriptive data and effect sizes at T2 of both immediate-SEIB group and delayed-SEIB group (receiving care as usual at T2). The preliminary effects of both immediate and delayed SEIB versions will be addressed by comparing descriptive data and effect sizes of the immediate-SEIB group at T2 and T3 to the delayed-SEIB group at T3 and T4.

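### The SEIB versus care-as-usual comparison at T2 has no baseline-adjusted between-arm estimate, although the primary outcome is measured at T1

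*Protocol article*

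**What the plan says.** All references are to the protocol article.

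- **Outcome.** Outcome Measures names traumatic stress as the expected primary outcome: "we anticipate the primary outcome of SEIB refers to traumatic stress symptoms of both parents/children".
- **Baseline data.** The same section limits baseline to two instruments per informant: "T1 will just comprise the use of two questionnaires: GHQ-12/SDQ and IES-R/CRIES-8". The primary outcome and psychological wellbeing therefore have a T1 score. Complicated grief, daily functioning as measured by the WSAS, social support, parenting and family functioning do not.
- **Allocation.** Recruitment and Randomization says when families learn their arm: "At the end of this first meeting, the families will receive a sealed opaque envelope". The visiting researchers do not know the allocation until then.
- **Size and purpose.** Sample Size and Statistical Analyzes says "we will recruit a total of 60 families (30 families in each group" and "Power analysis is not used to determine the final sample size". It also says "this study is not aimed to test SEIB effectiveness".
- **Analysis.** That section plans descriptive statistics with confidence intervals at all four time-points, a Cohen's d for between-group differences and a Cohen's d for change from baseline. Results are graded in fixed bands that start at 0.2. For the early effect it then says: "The preliminary early effects of SEIB will be addressed by comparing descriptive data and effect sizes at T2". It names no covariate and no baseline-adjusted estimate.

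**The concern.** With 30 families per arm, the arms can easily differ at T1 on the primary outcome by an amount that matters on the plan's own grading scale. A raw T2 difference carries a fraction of that T1 difference, equal to the T1–T2 correlation. It also leaves in the error term the outcome variance that T1 could explain.

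The change-from-baseline d does not solve this. If it is computed within each arm, two such values side by side are not a between-arm estimate. If change is compared between arms, it is less precise than adjustment, and less precise than the raw d when the correlation is below 0.5.

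Two things are at stake. One is the precision of the only randomised comparison of SEIB with care as usual, since the delayed arm starts SEIB after T2. The other is the stated aim of informing power calculations. A main trial sized for an adjusted analysis needs the T1–follow-up correlation or the residual SD, and the summary statistics listed (mean, percent, SD, range, confidence intervals) include neither.

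**Working it through.** **Inputs.** n = 30 per arm and the 0.2 threshold for a small effect come from Sample Size and Statistical Analyzes. The T1–T2 correlation r is not given, so it is an assumption, shown over 0.2 to 0.6. Complete follow-up is assumed.

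**The plan's own figure.** 30 per group × 2 groups = 60 families. This rests on a rule of thumb, so there is no power calculation to reproduce.

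**Is T1 a valid covariate?** It must precede knowledge of allocation. The envelope is opened at the end of the first meeting (Recruitment and Randomization). A researcher is with the family when T1 is filled in (Strengths and Limitations). The log written after the family visit covers both the envelopes and the questionnaires (Outcome Measures). Together these suggest that T1 is completed at the first meeting before disclosure. That is an inference; the article does not say so outright.

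**Step 1: chance imbalance at T1.** SE(d) ≈ √(2/n) = √(2/30) = 0.258. With a t distribution on 58 df:
- P(|T1 difference| ≥ 0.2 SD) = 44%
- P(≥ 0.3 SD) = 25%
- P(≥ 0.4 SD) = 12.7%

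**Step 2: what reaches the T2 result.** A T1 difference d0 shifts the expected raw T2 d by r × d0. For d0 = 0.2 the shift is 0.04, 0.06, 0.10 or 0.12 at r = 0.2, 0.3, 0.5 or 0.6. For d0 = 0.4 and r = 0.5 it is 0.20, which alone reaches the plan's threshold for a small effect.

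**Step 3: precision of three estimators at 30 per arm.**
- Raw T2 difference: SE = 0.258, 95% half-width 1.96 × 0.258 = 0.51.
- Adjusted for T1: SE = 0.258 × √(1 − r²); equivalent n = 30/(1 − r²).
- Between-arm difference in change: SE = 0.258 × √(2(1 − r)).

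| r (assumed) | Variance cut by adjustment (r²) | Adjusted SE | Adjusted half-width | Equivalent n per arm | Change-score SE |
|---|---|---|---|---|---|
| 0.2 | 4% | 0.253 | 0.50 | 31 | 0.327 |
| 0.3 | 9% | 0.246 | 0.48 | 33 | 0.305 |
| 0.5 | 25% | 0.224 | 0.44 | 40 | 0.258 |
| 0.6 | 36% | 0.207 | 0.41 | 47 | 0.231 |

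Estimating one covariate coefficient costs little: at r = 0.5 the half-width goes from 0.438 to 0.442.

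**Step 4: relevance to the main trial.** As an illustration only, take d = 0.5, two-sided 5% and 80% power, all assumed. The requirement is 63 per arm unadjusted, 58 at r = 0.3 and 48 at r = 0.5. The pilot can supply the r on which that difference depends.

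**Scope.** The 30 per arm counts families, so these figures fit the parent measures (IES-R, GHQ-12). Only children aged 12 to 18 are informants, and a family may supply none, one or several. The CRIES-8 and SDQ figures could differ.

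**The case against.** The strongest reply has four parts.

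- **T1 is not ignored.** A reader might infer that the plan discards the T1 scores. It does not: T1 descriptives with confidence intervals are planned, so imbalance would be visible, and a change d is planned and may be among the effect sizes compared at T2. This stands. What is missing is only an adjusted between-arm estimate.
- **The raw d is not biased.** A reader might infer from the 44% figure that the T2 result is wrong or biased. Randomisation keeps the raw d unbiased, and its SE already allows for chance imbalance. The 44% describes T1, and only r times the imbalance reaches T2. This also stands; the loss is in precision and conditional accuracy.
- **The gain may be small.** The article expects acute distress at T1 and impaired ability to complete questionnaires, which could weaken the T1–T2 correlation. At r = 0.2 the variance cut is only 4%. This stands as a limit on size. It does not favour the raw d, because the adjustment costs almost nothing at any r shown.
- **This is a descriptive pilot, and covariates belong in an analysis plan.** An article may leave model details elsewhere, and a document not shown may contain an adjusted analysis. But the article states which estimators address the early effect, so the point concerns a stated choice. Not testing hypotheses is no answer either, because the point concerns estimation and the inputs for a later sample size. It does keep the consequence moderate.

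**Conclusion.** The point holds as an improvement to a stated analysis choice. The T2 comparison of SEIB with care as usual is planned without a baseline-adjusted between-arm estimate, although T1 scores exist for the primary outcome and for wellbeing. For the parent measures the raw d has a 95% half-width of 0.51; adjustment would bring it to between 0.50 and 0.41 for r between 0.2 and 0.6. This rests on an assumed r, on 30 families per arm with complete follow-up, and on T1 being completed before allocation is disclosed.

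It does not extend to outcomes without a T1 score (ICG-19, IPG-A, WSAS, CSS, PCS, APQ, FAD). A reader might also want to carry the adjusted same-time contrast on to T3 and T4. That would not answer aim 6, which compares the immediate arm at T2 and T3 with the delayed arm at T3 and T4.

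**What to change.** For IES-R, GHQ-12, CRIES-8 and SDQ:

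1. Keep the raw T2 d. Beside it, report the T2 between-arm difference from a linear model with the T1 score as covariate, with a 95% CI, divided by the raw SD so that it stays on the d scale. Days since death at T1 may be added, because families can enter up to 3 weeks after the loss.
2. In the child models, allow for siblings in the same family.
3. Report the T1–T2 correlation and the residual SD as inputs for the main-trial sample size.
4. State explicitly that T1 is completed before the envelope is opened, if that is so.

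The cost is one extra model per outcome in the software already named, with no new data and no added burden on families.

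Suggested wording: *For measures collected at T1, the difference between groups at T2 will also be estimated with adjustment for the T1 score and reported with a 95% confidence interval, together with the T1–T2 correlation and the residual standard deviation.*

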## Introduction

Bereavement is a natural and common event, and most people are generally able to adapt to the resulting grief over time and regain function in their everyday life [1]. However, approximately 10% to 22% of bereaved people experience deleterious forms of mental distress that result in mental health deterioration [2]. The loss of a significantly loved person through death can be a complex and disturbing life event that is linked to greater psychological problems, physical illness, and mortality. Individual grief reactions can vary from minor and shorter responses to more severe and prolonged manifestations [3]. More importantly, unnatural and violent deaths significantly cause more severe after effects than natural deaths [4].

Complicated grief encloses the more severe and prolonged symptoms that hamper social and occupational functioning [3,5]. It has been found to be related to higher rates of mental disorders, sleep problems, suicidality, cardiovascular and cancer diseases, and lack of social support [6-10]. Preoccupied thoughts of the deceased, intense searching and yearning for the deceased, avoiding memories of the deceased, death denying, and crying are among the core symptomatology of complicated grief [11]. In addition, other comorbid symptoms that meet the criteria for depression and/or posttraumatic stress disorder (PTSD) have been documented [12].

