The present study aims to expand knowledge in early intervention on family -related psychological distress following a sudden and unexpected death of a partner/parent. It consists of a pilot study to assess the feasibility of a future main trial, as well as SEIB’s preliminary impact with suddenly bereaved families. Accordingly, the specific aims are to:

1. Assess recruitment materials and procedures.

2. Assess the usefulness of randomization and data collection materials.

3. Obtain reliable estimates regarding recruitment and retention.

4. Provide information on power calculations and possible outcomes (both parents and children).

5. Explore the 3-month SEIB effects' on traumatic stress symptoms, complicated grief symptoms, psychological wellbeing, daily functioning, social support, parental capacity, parenting practices, and family functioning, compared with the 3-month effects of care as usual.

6. Explore the 3- and 6-month effects of the immediate-SEIB version on traumatic stress symptoms, complicated grief symptoms, psychological wellbeing, daily functioning, social support, parental capacity, parenting practices, and family functioning, compared with the 6- and 9-month effects of the delayed-SEIB version.

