## Methods

### Trial Design

As outlined in Figure 1, this study is a one-center, pilot, randomized controlled trial (RCT) with a delayed intervention design in which suddenly bereaved families will be randomly assigned to: the immediate-SEIB intervention group (receiving SEIB in the aftermath of the loss) or the delayed-SEIB intervention group (control condition; receiving SEIB 3 months post loss). Both groups can make use of care as usual from their communities.

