### Participants and Eligibility Criteria

The sample will include bereaved families with children younger than 18 -years old, who suddenly and unexpectedly lose a partner and a parent. Bereaved partners and their children, aged from 12 - to 18 -years old, will be the informants of the study. To ensure a homogeneous sample, all family members must speak Norwegian. Eligible families are those who satisfy both of the criteria listed in Textbox 1.

Inclusion criteria.Criterion for unexpectedness: the loss shall occur following an accident, a suicide, a murder, or a disease, as well as situations where people are missing (presumed dead).Criterion for suddenness: the loss shall occur shortly, or within the same day as the event/disease happened or started. This period can be extended up to 5 days for people who do not regain consciousness after the incident (eg, illness/accident/suicide, etc). The families cannot enter this study later than 3 weeks after the death.

Potential participants with severe medical conditions for both bereaved partner and their children, such as serious physical impairment, intellectual deficit, severe child developmental problems, borderline personality disorder, history of psychosis (eg, schizophrenia, bipolar disorder), current substance use disorder (in the past 6 months), severe suicidal risk, or dementia will be excluded. Families receiving concurrent psychotherapeutic intervention for problems concerning loss and/or trauma will also be excluded.

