The rationale for both immediate-SEIB and delayed-SEIB versions relies on the need to minimize the initial misconceptions and maladaptive appraisals that may emerge in the aftermath of a traumatic event and that may exacerbate the onset of posttraumatic symptoms and complicated grief [27]. As a result, both immediate-SEIB and delayed-SEIB seek to enhance more appropriate coping responses that are expected to have an increasing effect over time. Also, early intervention may foster an open family climate that help the family to share facts and make decisions (eg, participating in rituals, school/work reentrance), favorable for them in a long-term perspective [27]. Traumatized parents tend to shield their children from facts, thus it seems important to stimulate proper levels of family communication, emotional expressiveness, and cohesion within the first weeks after a crisis event. This may decrease the individual and family arousal, increase family resilience, and stimulate a safer environment for trauma recovery [26]. These arguments constitute the base for our immediate-SEIB intervention and are in line with our clinical and research experience, showing bereaved people ask for immediate assistance [22,29]. The immediate-SEIB first follow-up period (session 4) is consistent with the International Classification of Diseases, suggesting that complicated grief meets its diagnostic criteria when the symptoms persist beyond 6 months after the death [43]. The immediate-SEIB second follow-up period (session 5) is consistent with the Diagnostic and Statistical Manual of Mental Disorders, requiring a minimum of 12 months [44].

The delayed-SEIB proposal is informed by the literature, given most preventive studies tend to start intervention within 2 to 6 months post loss [31,32]. For the delayed-SEIB intervention group, the first 3 sessions contain less advice on the acute handling of the situation (including children in rituals, return to work and school, securing social support) and less focus on reducing bodily activation by calming family members. They prioritize the traumatic aspects surrounding the death, and psychoeducation is adjusted to the reactions usually seen at this time-point (~3 months following the loss), when the unreality has abated and the social network is often less active in their support.

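### Aim 6 compares the two SEIB versions at visits 3 months apart in time since loss, so its effect sizes mix intervention timing with the natural course of grief

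*Protocol article*

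**What the plan says.** Specific aim 6 in the Introduction is to "Explore the 3- and 6-month effects of the immediate-SEIB version on traumatic stress symptoms" and the other outcomes, "compared with the 6- and 9-month effects of the delayed-SEIB version". Sample Size and Statistical Analyzes repeats this as the analysis: "comparing descriptive data and effect sizes of the immediate-SEIB group at T2 and T3 to the delayed-SEIB group at T3 and T4". The only same-visit contrast tied to a named aim is at T2, where SEIB is compared with care as usual (aim 5).

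One visit schedule serves both arms. Under Outcome Measures, "the families will be assessed at 4 time-points: baseline (T1), and after 3- (T2), 6- (T3), and 9-months (T4) follow-up". Under Participants and Eligibility Criteria, "The families cannot enter this study later than 3 weeks after the death". Trial Design describes the delayed arm as "control condition; receiving SEIB 3 months post loss", with care as usual open to both arms.

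On the expected course without SEIB, the Introduction says that "most people are generally able to adapt to the resulting grief over time", and Outcome Measures expects acute distress at T1. No rate of recovery is given. Strengths and Limitations credits the delayed design with exploring the effect of time. The limitations listed there do not mention that the paired visits differ in time since loss.

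**The concern.** Randomisation makes the arms comparable at the same point after the death. Aim 6 compares them at different points. If scores are still changing between 3 and 9 months after the loss, part of each difference would appear even if it made no difference when SEIB started.

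The best time to start is one of the study's two exploratory questions, and the effect sizes are to be graded small to very large as indices of clinical significance. A confidence interval shows imprecision but not this kind of bias. A main trial designed on these figures could be misled about when to begin.

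**Working it through.** **Inputs.** Visits are T1 at baseline and T2, T3 and T4 at 3, 6 and 9 months (Outcome Measures). Entry is within 3 weeks of the death (Participants and Eligibility Criteria). Delayed SEIB starts 3 months after the loss (Trial Design). There are 30 families per arm, and d of 0.2 or more is labelled small (Sample Size and Statistical Analyzes). The plan's own sample figure reproduces as 2 × 30 = 60. It comes from a rule of thumb and has no bearing on this comparison.

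**Step 1: line up the visits** (approximate months; entry within 3 weeks applies to both arms alike).

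| Contrast | Since loss, immediate v delayed | Since SEIB start, immediate v delayed |
|---|---|---|
| Planned: T2 v T3 | 3 v 6 | 3 v 3 |
| Planned: T3 v T4 | 6 v 9 | 6 v 6 |
| Same visit: T3 v T3 | 6 v 6 | 6 v 3 |
| Same visit: T4 v T4 | 9 v 9 | 9 v 6 |

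**Step 2: what each contrast estimates.** Let m(t) be the mean outcome in SD units t months after the loss without SEIB. Let eI(s) and eD(s) be the effects of the immediate and delayed versions s months after they start. Delayed minus immediate is then:

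- Planned pair 1: [m(6) − m(3)] + [eD(3) − eI(3)]
- Planned pair 2: [m(9) − m(6)] + [eD(6) − eI(6)]
- Same visit at T3: eD(3) − eI(6)
- Same visit at T4: eD(6) − eI(9)

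The first bracket in each planned pair is natural course. It cancels in the same-visit contrasts, which instead compare different lengths of time since SEIB start.

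**Step 3: change from baseline does not remove it.** Both arms start from T1, so the delayed arm's change includes its 3 months of care as usual. Only IES-R/CRIES-8 and GHQ-12/SDQ are collected at T1, so the other instruments have no baseline score.

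**Step 4: size, under an assumption.** Let r be the improvement in SD over the extra 3 months, with no true timing effect. The expected d is r in favour of delay. With one score per family, SE(d) ≈ √(2/30) = 0.258, and the 95% half-width is 1.96 × 0.258 = 0.51. The chance that the observed d reaches 0.2 in favour of delay is 1 − Φ((0.2 − r)/0.258).

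| Assumed r | Expected d for delay | Chance of d ≥ 0.2 for delay | A true 0.3 SD benefit of immediate SEIB shows as |
|---|---|---|---|
| 0 (same visit) | 0 | 22% | 0.3 |
| 0.1 | 0.1 | 35% | 0.2 |
| 0.2 | 0.2 | 50% | 0.1 |
| 0.3 | 0.3 | 65% | 0.0 |
| 0.4 | 0.4 | 78% | −0.1 |

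**Step 5: sensitivity.** Suppose recovery is exponential, D × 0.5^(t/h), with a total fall D of 0.5 to 1.5 SD and a half-life h of 3 to 12 months (also assumed). The bias is then 0.07 to 0.38 SD for T2 v T3 and 0.06 to 0.22 SD for T3 v T4. By the Step 4 formula, the second range gives a chance of about 29% to 53% of reaching 0.2. The later pair is probably the less affected.

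**The case against.** The pairing looks deliberate. Aim 6 concerns the two versions of SEIB, and matching on time since start gives each the same time to act. The same-visit contrast has its own imbalance: at T3 the immediate arm is about 6 months from starting and the delayed arm about 3, and sessions received may differ. Neither alignment isolates timing. This stands, and the fix must say so. The same-visit contrast does, however, compare the two randomised policies at equal time since loss.

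The article also plans descriptive statistics and confidence intervals for all outcomes at every visit, and between-group d without restricting it to particular visits. Same-visit figures could therefore be derived. But the text tied to aim 6 names only the staggered pairs.

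The study is a feasibility pilot that disclaims any test of effectiveness, and no decision rule rests on aim 6. This lowers the severity but does not remove the bias.

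A reader might infer more than the documents support:

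- **That the comparison always favours delay.** This holds only for outcomes that improve with time. The section Intervention says the social network is often less supportive by about 3 months, so perceived support may go the other way. No direction is documented for parenting or family functioning.
- **That the extra months are untreated.** Care as usual is available throughout.
- **That randomisation is lost.** The groups are still the randomised ones; what is given up is equal time since loss.
- **That the first pair straddles a diagnostic threshold for complicated grief.** The criterion "suggesting that complicated grief meets its diagnostic criteria when the symptoms persist beyond 6 months after the death" is cited to justify when session 4 is held. ICG-19 is analysed as a severity score.

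**Conclusion.** The point holds. Both statements of aim 6 set the delayed arm about 3 months further from the loss in each pair, so the effect sizes mix SEIB timing with natural course, and the article does not acknowledge this. The confounding follows from the article's own schedule and needs no outside figure.

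Its size does rest on an assumption. With recovery of 0.1 to 0.4 SD over 3 months and no timing effect, the expected d is 0.1 to 0.4 for delay. The small label is then reached in that direction about 35% to 78% of the time, against 22% at equal time since loss. These figures apply to outcomes that improve with time, with 30 scores per arm.

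It should be fixed, but a reader who concluded that it invalidates the trial would go too far. The aim is exploratory, the main purpose is feasibility, and the half-width of about 0.51 already limits what any d here can show.

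**What to change.** Reword aim 6 and the matching sentence in Sample Size and Statistical Analyzes so that the main comparison of the two timing policies is immediate versus delayed at T3 and again at T4. State that time since SEIB start, and possibly sessions received, then differ between arms. Keep T2 as SEIB versus care as usual.

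Retain the staggered pairs as secondary and descriptive. State the 3-month difference in time since loss in Strengths and Limitations, and do not interpret their d as an effect of timing.

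The cost is some rewording and a few more contrasts to report. Both arms already complete every instrument at T3 and T4, so no new data or families are needed.
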